#### ***Cell mediated immune response (CMI) analysis***

Descriptive analysis (mean, standard deviation, median, minimum and maximum) will be performed for the CMI endpoints. Graphical presentations of immune responses will be generated (Box-plots).

For intra-cellular staining (ICS) assays, the data will be presented as the frequency of CD4+ or CD8+ T cells per million PBMC expressing a given cytokine.

For ELISPOT assay, the data will be presented as the number of spots per million PBMC.

#### ***Immune response and vaccine efficacy***

The relationship between immune responses and vaccine efficacy will be explored and further detailed in the statistical analysis plan.

#### **10.8.4. Analysis of safety**

Safety analysis will be performed on the Total vaccinated cohort.

The percentage of subjects with at least one local AE (solicited and unsolicited), with at least one general AE (solicited and unsolicited) and with any AE during the solicited follow-up period will be tabulated with exact 95% CI after each vaccine dose and overall. The percentage of doses followed by at least one local AE (solicited and unsolicited), by at least one general AE (solicited and unsolicited) and by any AE will be tabulated over the entire vaccination course, with exact 95% CI.

The percentage of subjects reporting each individual solicited local and general AE during the 7-day (Day 0-Day 6) solicited follow-up period will be tabulated with exact 95% CI. The percentage of doses followed by each individual solicited local and general AE will be tabulated over the entire vaccination course, with exact 95% CI.

The same tabulation will be performed for grade 3 AEs and for AEs with relationship to vaccination. The verbatim reports of unsolicited symptoms will be reviewed by a physician and the signs and symptoms will be coded according to the MedDRA Dictionary for Adverse Reaction Terminology. The percentage of subjects with at least one report of unsolicited AE classified by the Medical Dictionary for Regulatory Activities (MedDRA) and reported up to 30 days (Day 0-Day 29) after vaccination will be tabulated with exact 95% CI. The same tabulation will be performed for grade 3 unsolicited AEs and for unsolicited AEs with a relationship to vaccination.

The number and percentage of subjects who took concomitant antipyretic/medication at least once during the 7-day (Day 0-Day 6) solicited follow-up period will be tabulated for each group, after each vaccine dose and overall, with exact 95% CI. The number and

percentage of doses for which the subjects took concomitant antipyretic/medication at least once during the 7-day (Day 0-Day 6) solicited follow-up period will be tabulated for each group, over the entire vaccination course, with exact 95% CI.

SAEs, AEs of specific interest and withdrawal due to AE(s)/SAE(s) will be described in detail.

Hematological (hemoglobin, WBC and platelets) and biochemical (creatinine, ALT and AST) laboratory values will be presented according to toxicity grading scales and tabulated by group.

Urine laboratory values will be tabulated by group.

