Preliminary clinical data with Ad35.CS.01 are available from a randomized, double-blind Phase I study carried out by the US National Institute of Allergy and Infectious Diseases, which evaluated the safety, tolerability and immunogenicity of increasing doses ( $10^8$  to  $10^{11}$  vp) of Ad35.CS.01. A total of 60 subjects (14, 15, 15 and 16 at the  $10^8$ ,  $10^9$ ,  $10^{10}$ , and  $10^{11}$  vp dose level, respectively) received vaccine, 12 subjects received a saline placebo at 0, 1, and 6 months.

The safety and tolerability of the Ad35.CS.01 malaria vaccine was evaluated through the assessment of local and systemic solicited reactions, unsolicited adverse events and clinical laboratory parameters.

The local tolerability of the vaccine was acceptable at all doses. The  $10^{11}$  vp dose was more frequently associated with pain of mild to moderate severity than the lower doses. The frequency of erythema was dose-dependent as well, but all the events were consistently mild across all doses. All solicited local reactions resolved without sequelae.

Systemic tolerability was assessed through the following solicited symptoms and signs: headache, malaise, myalgia, chill, nausea, vomiting and fever. Symptoms were scored

daily by subjects on diaries for 14 days after each dose. Results are summarized in [Table 1](#).

**Table 1** Number (%) of subjects with solicited systemic reactions, by maximal severity, after each injection

|             |          | Placebo
(N=12) | Ad35.CS.01 10 
(N= 14) | Ad35.CS.01 10 
(N=15) | Ad35.CS.01 10 
(N=15) | Ad35.CS.01 10 
(N=16) |
|-------------|----------|-------------------|---------------------------------------|--------------------------------------|---------------------------------------|---------------------------------------|
| First dose  | Mild     | 1 (8)             | 3 (21)                                | 2 (13)                               | 4 (27)                                | 6 (38)                                |
|             | Moderate | 2 (17)            | 2 (14)                                | 0 (0)                                | 1 (7)                                 | 5 (31)                                |
|             | Severe   | 0 (0)             | 0 (0)                                 | 0 (0)                                | 1 (7)                                 | 2 (13)                                |

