**Table 3 Study groups and epochs foreseen in the study**

| Study groups         | Number of subjects      | Age (Min/Max) | Epochs          |                   |                 |                 |
|----------------------|-------------------------|---------------|-----------------|-------------------|-----------------|-----------------|
|                      |                         |               | Screening epoch | Vaccination epoch | Challenge epoch | Follow-up epoch |
| RRR                  | 84                      | 18 - 50 years | x               | x                 | x               | x               |
| ARR                  | 84                      | 18 - 50 years | x               | x                 | x               | x               |
| Infectivity controls | 4 - 6 per challenge day | 18 - 50 years | x               |                   | x               | x               |

ARR = first dose with Ad35.CS.01, second and third doses with RTS,S/AS01B

RRR = three doses of RTS,S/AS01B

- Control: active control. The group receiving three doses of RTS,S/AS01B will be the comparator group. In addition, there will be infectivity controls for the challenge epoch (i.e. volunteers who will not receive any immunization but will be subjected to the sporozoite challenge).
- Vaccination schedule: 0-1-2 months followed by a challenge 21 days (3 weeks)  $\pm$  7 days after the third vaccination.
- Safety considerations:

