## **4. STUDY COHORT**

### **4.1. Number of subjects/centers**

The target enrollment for this study will be 168 healthy malaria-naïve adult subjects (84 subjects per group), to ensure 138 subjects will undergo sporozoite challenge (69 subjects per group), given an approximate 20% estimated drop-out rate, based on past experience. Additional volunteers to serve as infectivity controls will be enrolled. Between four to six control volunteers (not immunized) will be enrolled for each sporozoite challenge day.

Refer to Section [10.4](#) for a detailed description of the criteria used in the estimation of sample size.

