### Reactogenicity and Safety

- Handling of missing data:
  - Subjects who missed reporting symptoms (solicited/unsolicited or concomitant medications) will be treated as subjects without symptoms (solicited/unsolicited or concomitant medications, respectively). In case of significant non-compliance of study procedures for reporting symptoms, the analysis plan will be reassessed to ensure more accurate reporting of study data by further analysis.
  - For the analysis of solicited symptoms, missing or non-evaluable measurements will not be replaced. Therefore the analysis of the solicited symptoms based on the Total vaccinated cohort will include only subjects/doses with documented safety data (i.e. symptom screen/sheet completed).

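### Pooled per-dose AE percentages get exact 95% CIs that ignore repeated doses from the same subject, so with positive within-subject correlation those intervals, and only those, are too narrow

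*Protocol*

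**What the plan says.** Section 10.8.4 sets the population first: "Safety analysis will be performed on the Total vaccinated cohort". It then prescribes two kinds of tabulation, each with exact 95% CIs.

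- **Per subject.** For single symptoms: "The percentage of subjects reporting each individual solicited local and general AE during the 7-day (Day 0-Day 6) solicited follow-up period will be tabulated". For any local, general or any AE, and for antipyretic or medication use, the subject percentages are given after each dose and overall.
- **Per dose, pooled over the course.** For the composite categories, the row is "The percentage of doses followed by at least one local AE (solicited and unsolicited), by at least one general AE (solicited and unsolicited"); a third category covers AEs of either kind. For single symptoms: "The percentage of doses followed by each individual solicited local and general AE will be tabulated over the entire vaccination course, with exact 95% CI". A matching per-dose row is prescribed for antipyretic or medication use.

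The AE tabulations are repeated for grade 3 AEs and for AEs related to vaccination. Section 10.6 limits the solicited-symptom denominators: the analysis "will include only subjects/doses with documented safety data (i.e. symptom screen/sheet completed"). Nothing in Section 10 adjusts for several doses coming from one subject.

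**The concern.** An exact binomial interval is derived for independent trials with a common probability. In the pooled rows the trial is the dose, and one subject supplies up to three. A subject who reacts to one dose may well be likelier to react to the next; if so, 252 doses carry less information than 252 independent observations and the interval is too short.

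The occurrence of each solicited AE after each vaccination is a primary safety endpoint (Section 10.1), and this is the first trial to combine the two vaccines in one schedule (Section 1.2.1). At stake is how precisely the per-dose reaction rates in each group appear to be known.

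**Working it through.** The protocol gives no width or coverage for these intervals, so there is no stated figure to reproduce.

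**Inputs**

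- Subjects per group: "84 subjects per group" (Section 4.1).
- Doses per subject: three, from "Vaccination schedule: 0-1-2 months" (Section 3) and Table 22. Maximum doses per group: 84 × 3 = 252.
- Within-subject correlation: not stated. A range is used, with an indirect estimate from Table 1.

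**Step 1. What Table 1 suggests about correlation.** Table 1 reports "Number (%) of subjects with solicited systemic reactions, by maximal severity, after each injection", and also the counts after any dose. Adding mild, moderate and severe gives the number reacting after each dose. Under independence the expected number reacting at least once is N × [1 − (1 − p1)(1 − p2)(1 − p3)], adapted where N falls between doses. For placebo, the per-dose counts are 3, 5 and 2 of 12, so 12 × [1 − (9/12)(7/12)(10/12)] = 12 × 0.635 = 7.6, against 5 + 2 + 0 = 7 observed.

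| Group | Observed, any dose | Expected if doses independent |
|---|---|---|
| Placebo | 7 | 7.6 |
| 10^8 vp | 10 | 11.5 |
| 10^9 vp | 8 | 8.1 |
| 10^10 vp | 11 | 12.5 |
| 10^11 vp | 15 | 15.5 |
| Total | 51 | 55.3 |

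All five groups fall below expectation, as they would if the same people tend to react repeatedly. A latent-normal model with one common correlation reproduces the total of 51 at a latent correlation of 0.35. This corresponds to an ICC between binary outcomes of 0.21 at a 25% rate and 0.23 at 50%, so about 0.2.

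**Step 2. Width.** With three doses per subject and equal rates, the variance inflation is 1 + (3 − 1) × ICC = 1 + 2 × ICC. At ICC 0.2 this is 1.4, and the effective number of doses is 252 / 1.4 = 180. Clopper-Pearson intervals follow (widths computed before rounding the limits):

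| Per-dose rate | As prescribed, n = 252 | ICC 0.2, n = 180 | Width ratio |
|---|---|---|---|
| 50% | 43.7–56.3%, width 12.7 points | 42.5–57.5%, width 15.1 | 1.19 |
| 25% | 19.8–30.8%, width 11.0 | 18.9–32.0%, width 13.1 | 1.19 |
| 10% | 6.5–14.3%, width 7.8 | 6.0–15.3%, width 9.3 | 1.20 |

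**Step 3. Coverage.** This was simulated with 84 subjects × 3 doses, beta-binomial correlation, equal rates by dose (10%, 25%, 50%, 75%), and the Clopper-Pearson interval on 252 doses:

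| ICC | Coverage of the nominal 95% interval |
|---|---|
| 0 | 96–97% |
| 0.1 | 94–95% |
| 0.2 | 91–93% |
| 0.3 | 89–90% |
| 0.5 | 85–86% |

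**Step 4. Unequal rates by dose.** In ARR the first dose is a different product from the second and third, so rates may differ. Take 20%, 50% and 70% as an illustration (the protocol gives no such rates). The mean is 46.7%, and the pooled formula uses 0.467 × 0.533 = 0.249 per dose. The average of the three separate variances is (0.16 + 0.25 + 0.21) / 3 = 0.207. The formula therefore overstates the uncorrelated variance and offsets part of the clustering. Simulated coverage is 97% with no correlation and 94% at latent correlation 0.35, against 92% at the same correlation with equal 50% rates.

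**The case against.** The best defence has four parts.

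1. **The protocol never says that doses are independent, and Section 10.8 leaves detail to the statistical analysis plan.** This stands only in part. Section 10.8.4 already fixes both the denominator (doses) and the method (exact), so an analysis plan that follows it inherits the problem.
2. **Valid intervals stand beside the pooled ones.** This stands. A reader might infer that the reactogenicity intervals in general are too narrow. They are not: the per-subject tables, and the tables after each dose, count each subject once.
3. **Nothing depends on the pooled rows.** This also stands. A reader might infer that a comparison of ARR with RRR, or a safety decision, rests on these intervals. Section 10.8.4 plans no between-group safety test. The holding rules in Section 5.4.4.1.3 that are based on solicited AEs use percentages by dose number without CIs, and the dose 2 to dose 3 rule counts subjects. The AE power figures in Section 10.4 do not use these CIs. Judging the groups by overlap of intervals is not something the protocol proposes.
4. **The size can be exaggerated.** This stands. Assuming an ICC of 0.4 to 0.6 gives simulated coverage of 87–88% down to 83–84%, but nothing in the protocol supports values that high. Its only indirect evidence sits near 0.2. Unequal rates by dose shrink the shortfall, and 252 is a maximum: undocumented doses are excluded and some subjects will not receive all three, which lowers the inflation.

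**Conclusion.** The point holds for the pooled percentage-of-doses rows over the whole vaccination course, and for those only. As written, their exact 95% CIs treat up to three doses from one subject as independent and are too narrow if reactions are positively correlated within subject.

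At an ICC of about 0.2 and equal rates by dose, coverage is about 92% and the correct interval is about 20% wider. With strongly unequal rates, coverage is about 94% at the same latent correlation. The ICC is an assumption supported indirectly by Table 1, which rests on 12 to 16 subjects per group, homologous dosing of a single vaccine, and 14-day diaries where this trial uses 7 days. Figures for an ICC of 0.4 or more are assumption only.

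Severity is minor: the rows are descriptive, and sound per-subject intervals are prescribed in the same section.

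**What to change.** Add one sentence to Section 10.8.4. Keep exact CIs for the per-subject tables and for tables by dose number. For the pooled percentage-of-doses rows (any local, general or any AE; each solicited AE; their grade 3 and related versions; antipyretic or medication use), either use an interval clustered on subject, by GEE or sandwich variance or by a subject-level bootstrap, or report the percentage without a CI.

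The cost is slightly wider intervals in those rows and a small change to the table programs. No data, visits or subjects are added.

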## **11. ADMINISTRATIVE MATTERS**

To comply with ICH GCP administrative obligations relating to data collection, monitoring, archiving data, audits, confidentiality and publications must be fulfilled.

### **11.1. Remote Data Entry instructions**

Remote Data Entry (RDE), a validated computer application, will be used as the method for data collection.

In all cases, subject initials will not be collected nor transmitted to GSK. Subject data necessary for analysis and reporting will be entered/transmitted into a validated database or data system. Clinical data management will be performed in accordance with applicable GSK standards and data cleaning procedures.

While completed eCRFs are reviewed by a GSK Biologicals' Site Monitor at the study site, omissions or inconsistencies detected by subsequent eCRF review may necessitate clarification or correction of omissions or inconsistencies with documentation and approval by the investigator or appropriately qualified designee. In all cases, the investigator remains accountable for the study data.

The investigator and the partners will be provided with a CD-ROM of the final version of the data generated at the investigational site once the database is archived and the study report is complete and approved by all parties.

### **11.2. Monitoring by GSK Biologicals**

Monitoring visits by a GSK Site Monitor are for the purpose of confirming that GSK Biologicals' sponsored studies are being conducted in accordance with the ethical principles that have their origins in the Declaration of Helsinki and that are consistent with Good Clinical practice (GCP) and the applicable regulatory requirement(s) (verifying continuing compliance with the protocol, amendment(s), reviewing the investigational product accountability records, verifying that the site staff and facilities continue to be adequate to conduct the study).

The investigator must ensure provision of reasonable time, space and qualified personnel for monitoring visits.

Direct access to all study-site related and source data is mandatory for the purpose of monitoring review. The monitor will perform a RDE review and a Source Document Verification (SDV). By SDV we understand verifying RDE entries by comparing them with the source data that will be made available by the investigator for this purpose.

The Source Documentation Agreement Form describes the source data for the different data in the RDE. This document should be completed and signed by the site monitor and investigator and should be filed in the monitor's and investigator's study file. Any data item for which the RDE will serve as the source must be identified, agreed and documented in the source documentation agreement form.

For RDE, the monitor will mark completed and approved screens at each visit.

In accordance with applicable regulations, GCP, and GSK procedures, GSK monitors will contact the site prior to the start of the study to review with the site staff the protocol, study requirements, and their responsibilities to satisfy regulatory, ethical, and GSK requirements. When reviewing data collection procedures, the discussion will also include identification, agreement and documentation of data items for which the eCRF entries will serve as the source document.

GSK will monitor the study to verify that, amongst others, the:

- Data are authentic, accurate, and complete.
- Safety and rights of subjects are being protected.
- Study is conducted in accordance with the currently approved protocol and any amendments, any other study agreements, GCP and all applicable regulatory requirements.

The investigator and the head of the medical institution (where applicable) agrees to allow the monitor direct access to all relevant documents.

Upon completion or premature discontinuation of the study, the monitor will conduct site closure activities with the investigator or site staff, as appropriate, in accordance with applicable regulations, GCP, and GSK procedures.

### **11.3. Archiving of data at study sites**

Following closure of the study, the investigator must maintain all site study records in a safe and secure location. The records must be maintained to allow easy and timely retrieval, when needed (e.g. audit or inspection), and, whenever feasible, to allow any subsequent review of data in conjunction with assessment of the facility, supporting systems, and staff. Where permitted by applicable laws/regulations or institutional policy, some or all of these records can be maintained in a validated format other than hard copy (e.g. microfiche, scanned, electronic for studies with an eCRF); however, caution needs to be exercised before such action is taken. The investigator must assure that all

reproductions are legible and are a true and accurate copy of the original and meet accessibility and retrieval standards, including re-generating a hard copy, if required. Furthermore, the investigator must ensure there is an acceptable back-up of these reproductions and that an acceptable quality control process exists for making these reproductions.

GSK will inform the investigator/institution of the time period for retaining these records to comply with all applicable regulatory requirements. However, the investigator/institution should seek the written approval of the sponsor before proceeding with the disposal of these records. The minimum retention time will meet the strictest standard applicable to that site for the study, as dictated by ICH GCP, any institutional requirements or applicable laws or regulations, or GSK standards/procedures; otherwise, the minimum retention period will default to 15 years.

The investigator/institution must notify GSK of any changes in the archival arrangements, including, but not limited to, the following: archival at an off-site facility, transfer of ownership of the records in the event the investigator leaves the site.

#### **11.4. Audits**

To ensure compliance with GCP and all applicable regulatory requirements, GSK may conduct a quality assurance audit. Regulatory agencies may also conduct a regulatory inspection of this study. Such audits/inspections can occur at any time during or after completion of the study. If an audit or inspection occurs, the investigator and institution agree to allow the auditor/inspector direct access to all relevant documents and to allocate his/her time and the time of his/her staff to the auditor/inspector to discuss findings and any relevant issues.

#### **11.5. Posting of information on Clinicaltrials.gov**

Study information from this protocol will be posted on clinicaltrials.gov before enrolment of subjects begins.

#### **11.6. Ownership, confidentiality and publication**

##### **11.6.1. Ownership**

All information provided by GSK is and remains the sole property of GSK. The ownership of all data and information generated by the site as part of the study (other than a subject's medical records) is governed by the Clinical Trial Agreement (CTA) between the site, GSK, MVI and Crucell.

Ownership of all rights, title, and interests in any inventions, know-how or other intellectual or industrial property rights which are conceived or reduced to practice by site staff during the course of or as a result of the study is governed by the CTA.

